## Methods

This study protocol describes the design of a prospective, single-blinded RCT with an allocation ratio of 1:1, between CRFA and CRYO. Our main hypothesis is that substantial relief of pain would be achieved with both techniques (CRFA and CRYO) compared to baseline values and that both methods would be effective and tolerable in the intermediate management of KOA. (Fig. 1).

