Patients will discontinue all pain medications (opioids, NSAIDS, anti-depressants and anti-convulsant drugs), supplements, chondroprotective drugs, and other alternative therapies for KOA for 10 days prior to the screening/baseline visit. During follow-up, patients will be prohibited from undergoing any other adjunctive treatment for KOA, including steroid injections, viscosupplementation, and pain medications. Serious local complications from either CRFA or CRYO and the need for medications for pain relief will be a criterion for study discontinuity.

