### Outcomes

Patients will be assessed at baseline and 2-, 4-, 12-, and 24-weeks post-intervention (Table 1).

**Table 1 Tab1:** Timeline of the study

Timepoint	Enrollment		Allocation		Assessment times		
	− 3 w	− 1 w	0 w	2w	4 w	12 w	24 w
Enrollment							
Eligibility screening	√						
Informed consent	√						
Genicular nerve block		√					
Allocation			√				
Outcome measures							
NPRS (primary)			√	v	√	√	√
KOOS			√	–	v	√	√
OKS			√	–	v	√	√
PGIC			–	–	v	√	√
Complications medications			Intra-op				
			√	v	√	√	√
			√	v	√	√	√

*NPRS* Numerical Pain Rating Scale, *KOOS* Knee Injury and Osteoarthritis Outcome Score, *OKS* Oxford Knee Scores, *PGIC* Knee Patient Global Impression of Change

The primary outcome would be the efficacy of CRFA or CRYO at 2-, 4-, 12- and 24-weeks using the Numerical Rating Pain Scale (NRPS). The secondary outcomes will be the potential improvement of the KOOS, and OKS at 12- and 24-weeks post-intervention. Patients will be also asked about their impression of improvement using the 7-point scale of Patient Global Impression of Change (PGIC) [34]; PGIC responders are the patients who indicate that they are either “very much improved” or “much improved” at each follow-up assessment. Expected side effects and complications (for example, bruising, swelling, numbness, inflammation, and/or erythema) involving percutaneous access to the nerves and the use of local anesthesia will be assessed at each follow-up visit and documented independently, except for loss of motor function outside the treatment area. The details of the timeline, assessments, and follow-up evaluations are presented in Table 1.

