### Sample size

According to the protocol, the patients will be randomly assigned into two groups, and they will all be evaluated (with NPRS) four more times after the baseline assessment (15 days, 4 weeks, 12 weeks, and 24 weeks, post-intervention). The main objective is to examine the possible diversity in NPRS (primary outcome) improvement among patients in different groups. The regular statistical approach to do this is to perform repeated measures ANOVA (rmANOVA), taking as given that all ANOVA assumptions are met (for example, normality of scores). Thus, the statistical power analysis for an rmANOVA procedure is as follows: we, as a priori, assume a number of groups equal to two and a number of measurements (except baseline) equal to four. More specifically, the NPRS is expected to be reduced in the two groups (CRYO and CRFA) at least 30%, relative to baseline assessment. According to Cohen [35], this fact denotes a medium effect size of approximately 0.50. Statistical significance is usually considered at the 5% level, and the power analysis curve for the rmANOVA is shown in Fig. 3. This figure illustrates that approximately 47 patients suffice for an achieved power of 80% using rmANOVA, taking into account a moderate effect size and 62 patients for 90% statistical power. Considering a 10% loss of follow up, we will enroll 70 patients in the study.

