### Data collection and management

Data will be collected in paper forms at baseline and 2-, 4-, 12-, and 24-weeks post-intervention. Quality assessments and proper training sessions will be conducted to ensure that all information is collected properly. Outcome data include the NPRS, KOOS, OKS, and PGIC, all of which are patient-reported questionnaires. Demographic data, radiographs (downloaded from PACS and saved in JPEG format), and intraoperative pictures of skin marks or videos from the interventions will also be collected. A hard copy folder will be created for each patient, including all paper forms, demographic data, and intervention details. These folders will be kept safe in the hospital office of the primary investigator ([name]) inside a special locker. The other main investigator ([name]) will transfer all the data into an Excel database using the desktop computer at the office of the primary investigator ([name]). Patient identification will be performed using only the national insurance number (11-digit number). Excel forms without patient names will be used for data analysis. Paper forms and computerized data could be assessed only by the two primary investigators. These files will be kept for at least three years after the last enrolled patient for future expansion of the research. We are not expecting participants to discontinue or deviate from the primary intervention. The coordinator nurse will be responsible for contacting them for missing appointments of clinical evaluation, either by phone or email. In case of refusal to attend, we plan to send the questionnaires by mail or make home visits. No other efforts will be made to minimize the loss of follow-up. Missing data from more than one time point will be a reason for dropout from the study.

Data entry, coding, security, storage, assessment of quality and creation of Excel tables will be under the responsibility of the two main investigators. Excel database would be password-protected. Personal information about potential and enrolled participants before, during, and after the trial will be collected to ensure confidentiality (using only the national insurance number as an indicator).

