### Statistical methods

The sample size and power in the study have been previously described. Another statistical approach for the study is to evaluate all follow-up (post-intervention) measurements separately from the baseline. This may occur in two possible ways: one with the use of an ANCOVA procedure and the other with the use of ANOVA on the difference in the scores (follow-up minus the baseline). As Borm et al. [36] suggested, the ANCOVA approach requires a significantly smaller number of participants, reduced by a multiplicative factor that depends on the correlation estimate between the prior and posterior scores, which is usually high. More specifically, a significance level of 5% along with a power of 80% is achieved with 24–45 patients in total, when the correlation estimates between the a priori and a posteriori score is approximately 80–90%, which is a realistic approach. To sum up with the statistical plan, longitudinal (that is, repeated measures) analysis will be conducted with repeated measures ANOVA. Furthermore, the slopes of the score trajectories (trendlines) will be compared among the two patient groups using 1-way ANOVA. Bivariate comparisons for baseline versus follow-up will be conducted using ANCOVA. 1-way ANOVA will assist in detecting variations in bivariate differences of scores (baseline versus each follow-up) among the two patient groups. Data will be reported as differences between group means (means ± standard deviations, 95% CIs) if normal distributed, otherwise as medians with interquartile ranges. Categorical data will be reported as numbers and proportions. A statistically significant difference of at least two in NPRS scores between groups, will be interpreted as a minimal clinically important difference (MCID). The statistical method of pairwise (available case analysis—ACA) deletion will be used for missing data at only one time point. If more than two time points are missed the list-wise (Complete-case analysis—CCA) deletion method will be used. Statistical analysis will be performed using R language and Rstudio IDE, two well-known open-source products.

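### If needing pain medication ends NPRS collection, as the rule most naturally reads, later improvement from baseline within each arm is overstated

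*Protocol article*

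**What the plan says.** The last paragraph of the CRYO technique section sets a medication rule for both arms: "During follow-up, patients will be prohibited from undergoing any other adjunctive treatment for KOA, including steroid injections, viscosupplementation, and pain medications". It then says that "the need for medications for pain relief will be a criterion for study discontinuity", alongside serious local complications.

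Pain on the NPRS at 2, 4, 12 and 24 weeks is the primary outcome (Outcomes). The opening of Methods gives the main hypothesis as a within-arm one: "substantial relief of pain would be achieved with both techniques (CRFA and CRYO) compared to baseline values". Sample size gives the main objective as comparing NPRS improvement between the groups.

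Missing scores are covered twice. Data collection and management says: "Missing data from more than one time point will be a reason for dropout from the study". Statistical methods says that pairwise "deletion will be used for missing data at only one time point", with list-wise deletion when more than two are missed.

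Three places bear on whether scores continue. Sample size says of the patients that "they will all be evaluated (with NPRS) four more times after the baseline assessment". Table 1 appears to record medications at each visit. Data collection and management offers mailed questionnaires or home visits to patients who refuse to attend. None mentions patients discontinued for needing analgesics.

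**The concern.** CRFA and CRYO are each delivered in one session, so there is no continuing treatment to withdraw. A discontinuation rule triggered by needing pain relief therefore acts on participation, and its trigger is close to a poor value of the primary outcome. The plan's handling of gaps, dropout or deletion, averages whoever remains.

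What is at stake is the within-arm hypothesis. There is no sham or untreated arm to offset a selective loss of patients in pain, and scores never collected cannot be recovered by any later analysis. The rule could well be used: Recruitment describes a pool that includes patients who have not responded to oral medication, and all analgesics are stopped before baseline.

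**Working it through.** **The plan's own figure.** Sample size gives 47 patients for 80% power, 62 for 90%, and 70 enrolled. A repeated measures ANOVA with two groups, f = 0.50, alpha 0.05 and noncentrality f²N needs 48 and 61 (four measurements, df2 = N − 2) or 49 and 63 (five measurements, df2 = 4(N − 2)). Then 62/0.9 = 68.9, so 69 against 70. The sample size reproduces closely and is not at issue. The 10% allowance replaces numbers; it does not correct selective loss.

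**How the rules act together.** A patient stopped after week 2 misses three visits, which means dropout and list-wise deletion. One stopped after week 4 misses two, which means dropout. One stopped after week 12 misses one, which means pairwise deletion. In each case the missing score is simply left out.

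**Direction.** If a fraction p is removed, then

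improvement in those remaining − improvement in all = p × (mean improvement of those remaining − mean improvement of those removed).

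For a gap of 1 to 4 points this is 0.1–0.4 at p = 10%, 0.2–0.8 at 20% and 0.3–1.2 at 30%. It is positive whenever those removed improved less.

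**Illustrative size.** Inputs:
- Baseline mean 6.9, baseline SD 0.8 and follow-up SD 2.4, from the CRFA versus hyaluronic acid trial cited in the Discussion. Baseline SDs of 1.5 and 2.0 are assumed as alternatives.
- Baseline/follow-up correlation 0.8–0.9, since Statistical methods says "the correlation estimates between the a priori and a posteriori score is approximately 80–90"%. Correlation between follow-up visits 0.7 or 0.85 (assumed).
- Follow-up mean 4.83 = 6.9 × 0.70, the 30% reduction in Sample size, which is a floor; or 2.8, the cited 12-month mean.
- Removal after weeks 2, 4 or 12 when NPRS is 7 or more, with probability 0.5–1 (assumed).
- Scores rounded and limited to 0–10, baseline at least 4, 400,000 simulated patients per setting.

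Change at week 24 among those remaining:

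| Follow-up mean | Removed | True | Reads | Overstated by |
|---|---|---|---|---|
| 4.83 | 25–42% | 2.02–2.07 | 2.11–2.87 | 3–39% |
| 4.83 | held to 10% | 2.02–2.07 | 2.06–2.26 | 1–9% |
| 2.8 | 7–13% | 3.96–3.98 | 4.02–4.24 | 1–7% |
| 2.8 | held to 10% | 3.96–3.98 | 4.03–4.23 | 1–7% |

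In the first row, at correlation 0.8, the overstatement is 21–39% with baseline SD 0.8, 10–24% with 1.5 and 3–16% with 2.0. A cut-off of 6 or 8 gives 4–56% or 3–25%. Averaged over the four visits, using every score collected before removal, it is 2–25% at mean 4.83 and 1–4% at mean 2.8; week 2 is then unaffected.

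A cruder model with a fixed baseline and between-visit correlation 0.6 gives 2.34 against 2.10 at 10% removed (0.24/2.10 = 11%) and 2.53 against 2.09 at 20%. It runs slightly higher because those removed have no higher baseline to offset their later pain.

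**Between arms (cut-off 7 in both).** With equal means the difference stays within 0.01 of zero. With means 3 and 4, a full-data difference of 0.92–0.96 reads 0.68–0.94 on change scores and 0.75–0.93 by ANCOVA. Only an assumed split of cut-offs, 6 in one arm and 8 in the other, turns a true zero into 0.02–0.37 (change) or 0.05–0.26 (ANCOVA).

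**Continued follow-up under analgesia.** If analgesics lower the week 24 score by 1–2 points, mean improvement reads 2.28–2.88 against 2.02–2.07. An arm difference of 0.92–0.95 reads 0.68–0.87, against 0.69–0.94 under the current rule (correlation 0.8). The share with at least a 30% reduction, at mean 4.83, is truly 46–48%. Among patients left under the current rule it is 54–68%; with analgesic use counted as failure it is 33–45%.

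**The case against.** The strongest reply is that the article never says assessments stop. All patients are to be evaluated four times, medications appear in Table 1, and mail or home visits are planned. A condensed article may leave follow-up after discontinuation to the full protocol. This is why the point is conditional. It does not remove it: the rule itself is stated, and those three provisions describe the schedule, the recording of use and missed appointments without exempting discontinued patients.

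Second, the stated main objective is the between-group comparison, where the rule is neutral or attenuating under similar rescue behaviour. That stands. A reader might infer that the rule can manufacture a difference between CRFA and CRYO. The documents do not support this, since nothing in them says rescue behaviour differs by arm.

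Third, a reader might take 39% as the expected bias. It is not. The setting that produces it pairs near-certain removal at the cut-off with baseline SD 0.8 at week 24, whereas the plan allows 10% loss and expects no one to discontinue. At 10%, the most is 0.092 × 2.07 = 0.19 points, small beside the plan's 2-point MCID. The MCID is a between-group threshold, however, so it does not settle the within-arm claim.

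Fourth, continued follow-up alone does not isolate the procedure's effect, and in some settings its mean lies further from the truth than under the current rule. This also stands, and it shapes the fix. Preferring pain without analgesics is a legitimate aim, but deleting patients who need them does not estimate it.

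**Conclusion.** The point holds conditionally and should be fixed. If needing analgesics ends NPRS collection, later within-arm improvement is overstated, because patients with worse pain leave and their scores are deleted. The direction rests only on those removed having improved less. The size cannot be fixed from the article: about 1–9% at week 24 if removals stay within the planned 10%, more only with heavier removal, and less at earlier visits as long as scores already collected are kept. If list-wise deletion discards a removed patient's early scores too, those visits are also affected.

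The between-arm difference is unbiased with equal arms and equal rescue behaviour, attenuated when the arms differ with a similar threshold, and inflated only if rescue behaviour differs by arm. Confidence is medium, because the step from study discontinuity to lost scores is a reading of the wording and the rate of analgesic need is unknown.

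**What to change.** State that needing analgesics or other adjunctive treatment does not end follow-up. Collect NPRS, KOOS, OKS and PGIC at all their scheduled visits for every randomised patient, record medication use at each visit as Table 1 already appears to intend, and analyse all patients as randomised. Whether analgesics are allowed remains a clinical decision for the investigators.

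Beside the mean NPRS result, report a named responder analysis in which analgesic use counts as non-response, for example at least a 30% NPRS reduction without analgesics. The two belong together: the mean then describes the procedure plus rescue as needed and can flatter the procedure, while the responder analysis errs on the cautious side.

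The cost is one clarifying sentence and one further analysis, with no extra patients or visits. The downside is that some scores will be recorded under analgesia.

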### Outcomes

Patients will be assessed at baseline and 2-, 4-, 12-, and 24-weeks post-intervention (Table 1).

**Table 1 Tab1:** Timeline of the study

Timepoint	Enrollment		Allocation		Assessment times		
	− 3 w	− 1 w	0 w	2w	4 w	12 w	24 w
Enrollment							
Eligibility screening	√						
Informed consent	√						
Genicular nerve block		√					
Allocation			√				
Outcome measures							
NPRS (primary)			√	v	√	√	√
KOOS			√	–	v	√	√
OKS			√	–	v	√	√
PGIC			–	–	v	√	√
Complications medications			Intra-op				
			√	v	√	√	√
			√	v	√	√	√

*NPRS* Numerical Pain Rating Scale, *KOOS* Knee Injury and Osteoarthritis Outcome Score, *OKS* Oxford Knee Scores, *PGIC* Knee Patient Global Impression of Change

The primary outcome would be the efficacy of CRFA or CRYO at 2-, 4-, 12- and 24-weeks using the Numerical Rating Pain Scale (NRPS). The secondary outcomes will be the potential improvement of the KOOS, and OKS at 12- and 24-weeks post-intervention. Patients will be also asked about their impression of improvement using the 7-point scale of Patient Global Impression of Change (PGIC) [34]; PGIC responders are the patients who indicate that they are either “very much improved” or “much improved” at each follow-up assessment. Expected side effects and complications (for example, bruising, swelling, numbness, inflammation, and/or erythema) involving percutaneous access to the nerves and the use of local anesthesia will be assessed at each follow-up visit and documented independently, except for loss of motor function outside the treatment area. The details of the timeline, assessments, and follow-up evaluations are presented in Table 1.

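### The primary outcome is NPRS at four visits with none primary, and four overlapping analyses are planned without saying which result decides

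*Protocol article*

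**What the plan says.** The Abstract, the Introduction and the Outcomes section all define the primary outcome in the same way: "The primary outcome would be the efficacy of CRFA or CRYO at 2-, 4-, 12- and 24-weeks using the Numerical Rating Pain Scale (NRPS". None of them singles out a visit.

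The Sample size section gives the between-arm aim: "The main objective is to examine the possible diversity in NPRS (primary outcome) improvement among patients in different groups". It calls repeated-measures ANOVA (rmANOVA) the regular way to pursue that aim and sizes the trial on it: "we, as a priori, assume a number of groups equal to two and a number of measurements (except baseline) equal to four". On the error rate it says only: "Statistical significance is usually considered at the 5% level". The result is 47 patients for 80% power and 62 for 90%, with 70 enrolled. The section does not say whether the powered test is group, time or interaction.

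Statistical methods offers a second approach, evaluating follow-ups separately from baseline. It has its own sample size: 24–45 patients at 5% and 80% power, with a correlation of 0.8–0.9. The summing-up lists rmANOVA first and then adds three analyses:
- The first looks at trajectories over time: "the slopes of the score trajectories (trendlines) will be compared among the two patient groups using 1-way ANOVA".
- The second takes single visits and brings in the starting score: "Bivariate comparisons for baseline versus follow-up will be conducted using ANCOVA".
- The third works on change scores and has a supporting role: "1-way ANOVA will assist in detecting variations in bivariate differences of scores". It is applied at every follow-up and sets one arm against the other.

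The article does not rank these analyses or divide the 5% among them. The 2-point relevance threshold names no visit. The opening of Methods states the main hypothesis differently, as relief from baseline with both techniques.

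**The concern.** With four visits and four methods on one outcome, the article does not tell a reader which number will be the trial's answer. Several results could be presented as the primary finding, and no rule says which prevails if they disagree.

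Disagreement is plausible here. The Introduction says that nerves regenerate after CRYO whereas CRFA ablates them completely, and Strengths and limitations says the CRYO mechanism might attenuate effects. Early and late contrasts may therefore differ, and the choice of visit could change the conclusion.

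Two of the added analyses also contribute little. Change-score ANOVA repeats the ANCOVA contrast, and a straight-line slope suits an early drop followed by a plateau poorly.

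**Working it through.** **1. The plan's own figures.**
- rmANOVA: noncentral F with λ = f²N, f = 0.50, α = 0.05, two groups. For a time or interaction effect, N is 45 (80%) and 59 (90%) with four measurements, and 49 and 63 with five (baseline included). The stated 47 and 62 lie between. For the group effect the same formula gives 34 and 45. The figures therefore fit a time or interaction test, but this formula gives the same N for both, so they cannot show which was meant.
- The rationale does not settle it. The statement "this fact denotes a medium effect size of approximately 0.50" rests on an expected reduction of at least 30% from baseline in both arms, which is a change over time and not a difference between arms.
- ANCOVA: a standardised difference of 0.50 needs 63 per arm. The total is 126 × (1 − r²), which is 126 × 0.36 = 45.4 at r = 0.8 and 126 × 0.19 = 23.9 at r = 0.9. This matches 24–45.

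**2. Count of between-arm tests.** rmANOVA group and interaction (2) + slope (1) + ANCOVA at four visits (4) + change score at four visits (4) = 11. This reads the ANCOVA sentence as one between-arm comparison per visit.

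**3. False-positive rate under no difference.** The simulation used 31 per arm (62/2), normal scores, 20,000 trials per setting and each test at p < 0.05. rmANOVA was run on the four follow-ups with Greenhouse–Geisser correction, and slopes were fitted to all five time points. The article gives only a baseline–follow-up correlation (0.8–0.9), so correlations are assumed: compound symmetry 0.3–0.9, AR(1) 0.5–0.9, and baseline 0.3 with follow-ups correlated 0.6 or 0.8.

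| What may be claimed | Chance of at least one p < 0.05 |
|---|---|
| One named rmANOVA effect | 5% (nominal) |
| rmANOVA group or interaction | 9.0–9.9% |
| Any of four ANCOVAs | 12.0–17.6% |
| Any of the 11 tests | 21.5–28.0% |

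For reference, four independent tests give 1 − 0.95⁴ = 18.5%. All 11 tests on mutually independent scores gave 30%. The interim look described in the article is not included.

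**4. ANCOVA against change score.** With equal variances, the variance of the between-arm estimate is proportional to 1 − r² for ANCOVA and to 2(1 − r) for change scores. The ratio is (1 + r)/2: 0.65 at r = 0.3, 0.90 at r = 0.8 and 0.95 at r = 0.9. It never exceeds 1, so the change score is less precise or at best equal.

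**5. Slope.** Take a constant 2-point advantage at every follow-up.
- Follow-up visits only: the lines are parallel and the slope difference is 0.
- Weeks 0, 2, 4, 12, 24: mean 42/5 = 8.4; Sxx = 740 − 5 × 8.4² = 387.2; slope difference = 2 × 8.4/387.2 = 0.043 points per week.

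**The case against.** The strongest reply is that a main analysis can be inferred. Sample size ties the stated objective and the whole enrolment figure to rmANOVA. Statistical methods lists it first, introduces slopes as an addition and gives change-score ANOVA an assisting role. rmANOVA also covers the four visits in one model. This stands: a reader might infer that the plan has no main analysis at all, and the text does not support that. What remains is that rmANOVA is implied and not declared, and its effect is unnamed. A significant interaction would still not say which visit or arm is favoured.

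Other inferences also go too far:
- **Every test is run at 5%, so the trial's error rate is several times a stated one.** The 5% level appears only in the power text. The article states neither a per-test rule nor a trial-wide rate, so the inflation is conditional on what may be claimed.
- **Any significant result would count as success.** The article interprets a significant difference of at least 2 points as clinically important. If that were required, chance findings over four visits would be about 0.2–2%, assuming SD 2.4–2.8 (the CRFA values quoted in the Discussion), 31–35 per arm and independent visits. But it is offered as an interpretation, not as a success rule.
- **rmANOVA discards baseline.** Excluding baseline from the count of four describes the power calculation. The analysis model is not specified, and the stated 47 and 62 are if anything closer to five measurements.
- **The slope test cannot see a constant benefit.** That is so only if baseline is left out of the slope, which the article does not say.

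A multiplicity rule may sit in an analysis plan not shown, so its absence alone is no finding. The primary visit and deciding comparison are different: the article itself sets out four visits and four methods and leaves the choice among them open.

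**Conclusion.** The concern holds in a limited form. No visit is primary, and four overlapping analyses are listed without a declared deciding one. rmANOVA is the implied main analysis, but its tested effect is not named, and the article's two statements of purpose (relief from baseline in both arms; difference between arms) point to different effects.

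The size depends on the rule eventually applied: 5% if one rmANOVA effect is named, about 9–10% if group or interaction may count, about 12–18% if any of four ANCOVAs may count, and about 21–28% if any method may. These figures rest on normal scores, 31 per arm, the assumed correlations and the 11-test count. The text does not say that the most permissive rule will be used, but it does not exclude it either. The redundancy of the change-score analysis holds whatever the correlation. The weakness of the slope is secondary, and its degree depends on whether baseline is included.

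**What to change.** Before unblinded results are seen, declare one primary between-arm contrast. The CRFA–CRYO difference in NPRS at 24 weeks would match the stated six-month horizon. That horizon describes the length of follow-up and does not itself make 24 weeks primary, so another single visit named by the sponsor would serve.

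Estimate the contrast with a 95% CI from one repeated-measures model with arm, visit, arm-by-visit, baseline NPRS and baseline-by-visit. Report the other visits from the same model as secondary, in a fixed order. Label the slope and change-score analyses exploratory. State that the primary question is the difference between arms, and report relief from baseline within each arm separately.

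The sponsor gives up the choice of headline visit and must restate the power. The 47/62 figures were computed for rmANOVA, and 24–45 assumes a correlation of 0.8–0.9. By the same ANCOVA formula a correlation of 0.5 needs 126 × 0.75 ≈ 95 patients and 0.3 needs 126 × 0.91 ≈ 115, against 70 × 0.9 = 63 expected to remain. The correlation assumption therefore needs support.
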